## The level of significance and power of the clinical study

It is not known if the REBOA can only be of benefit, it is also possible that it may decrease the chance of good outcome. Therefore, a two-sided test with significance level of 0.05 is chosen in the analyses. On the interim analysis, a significance level following the O´Brien-Fleming approach is chosen ^45,46^.

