## Interim analyses

Three interim analyses will be performed, after 30, 60 and 90 patients in both the intervention and the control group is included. No specific time schedule for interim analyses is set. The important variables to assess is the primary endpoint and 30-day survival with good neurologic outcome.

We will consider recommending the sponsor to stop the trial after interim analysis if there is a difference in primary endpoint or 30-day survival between the groups, with a significance level following the O´Brien-Fleming approach ^45,46^.

From the second interim analysis, we will perform a sample size calculation, based on the assumption that the current difference in primary endpoint between the two groups will persist. If the sample size needed to prove a difference is more than three times the planned sample size (with 0.80 power and a significance level of 0.05), we would consider recommending the sponsor to stop the trial due to futility.

On the last interim analysis, we will re-estimate the sample size in case of a non-significant difference on the primary endpoint. If the estimated sample size needed to prove a difference between the groups is above 100, but equal to or less than 150 in each group (with 0.80 power and a significance level of 0.05), the final sample size will be modified and we would recommend the sponsor to continue the trial until the modified sample size is reached.

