## Trial Discontinuation

The whole trial may be discontinued at the discretion of the sponsor in the event of any of the following:

- Occurrence of adverse events unknown to date in respect of their nature, severity and duration
- Medical or ethical reasons affecting the continued performance of the trial
- Difficulties in the recruitment of patients
- Changes in funding

If the interim analysis report significant group difference in primary endpoint, the study can be stopped. A recommendation to the sponsor to stop the study will only happen after a face to face meeting of the project management.

The study may be suspended or terminated by a site investigator at any time. The SI can only suspend or terminate the study at his/her study site.

The study may be suspended or terminated if serious safety issues are raised. This includes malfunction of equipment, indications of misuse of equipment or inappropriate performance skills in one or more of the physicians.

The data monitoring committee can recommend the sponsor to suspend or terminate the study if they find grave and unsolvable safety issues.

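### Section 9.6 does not say that 0.05 covers all looks (about 5.7% error for ROSC if the final test uses 0.05), and the efficacy stopping endpoint differs between chapter 9, 9.3 and 11.3

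*Protocol*

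**What the plan says.** **Level.** Section 9.6 states that "a two-sided test with significance level of 0.05 is chosen in the analyses". For the interim analysis it adds that "a significance level following the O´Brien-Fleming approach is chosen". No section gives a final critical value or calls 0.05 the overall error across looks. The sample size (9.2), the futility rule and the sample size re-estimation (both 9.3) all use 0.05 without adjustment.

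**Looks.** Section 9.3: "Three interim analyses will be performed, after 30, 60 and 90 patients in both the intervention and the control group is included". The planned final size is 100 per group.

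**Stopping endpoint.** Section 9.3 first says "The important variables to assess is the primary endpoint and 30-day survival with good neurologic outcome". It then says that a stop will be considered "if there is a difference in primary endpoint or 30-day survival between the groups", at O'Brien-Fleming levels. The opening of chapter 9 also names the primary endpoint or the 30-day survival rate. Section 11.3 names one endpoint: "If the interim analysis report significant group difference in primary endpoint, the study can be stopped".

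**Route.** Section 11.3: "A recommendation to the sponsor to stop the study will only happen after a face to face meeting of the project management". In the same section, the DMC may recommend suspension or termination for grave safety problems; no efficacy role is given to it there.

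**The concern.** O'Brien-Fleming boundaries hold a trial at 5% only if the final test is part of the scheme. The third look comes at 90% of the planned information, so much of the error has been spent before the final test. If that test is still run at 0.05, a final p-value between about 0.041 and 0.05 would be called significant although a design held at 5% overall does not support it.

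The stopping endpoint is a separate matter. Read together, the sections leave open whether a survival difference can stop the trial, and whether survival means being alive at 30 days or being alive with mRS 0-3. Two endpoints tested at the same interim levels, with no split of alpha, give two chances of a false crossing.

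The trial is open-label for those who treat, and the project management group runs it from day to day. Requiring that group to meet before any stop recommendation leaves open whether it would see comparative results while recruitment continues.

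**Working it through.** **Inputs.** From the protocol: two-sided 0.05 (9.6); looks at 30, 60 and 90 per group (9.3); final at 100 per group, ROSC 18% versus 36%, power 0.80 (9.2). Information fractions are t = 0.3, 0.6, 0.9 and 1.0.

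**The plan's own figure.** Pooled-variance formula: n = [1.960·√(2·0.27·0.73) + 0.842·√(0.18·0.82 + 0.36·0.64)]² / 0.18² = (1.231 + 0.517)² / 0.0324 = 94.3. The stated 94 per group is reproduced (95 if rounded up; power at 94 is 0.799). It is a single-look figure with no allowance for interim tests.

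**O'Brien-Fleming held at 5% overall.** Boundaries are z = C/√t. Recursive numerical integration at the four fractions gives C = 2.046.

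| Per group | z | Nominal two-sided p | Error spent at this look |
|---|---|---|---|
| 30 | 3.735 | 0.00019 | 0.0002 |
| 60 | 2.641 | 0.0083 | 0.0081 |
| 90 | 2.157 | 0.0310 | 0.0256 |
| 100 | 2.046 | 0.0408 | 0.0161 |

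The three interim looks spend 0.0002 + 0.0081 + 0.0256 = 0.0339; the final look brings the total to 0.050.

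**Same interim boundaries, final test at 0.05 (z = 1.960).** The final look now spends 0.0232, so the total is 0.0339 + 0.0232 = 0.0571. Other boundary choices:
- Lan-DeMets spending of O'Brien-Fleming type: 0.058 to 0.060, depending on how the two-sided function is written. Its corrected final level is 0.036 to 0.039.
- Levels for four equally spaced looks (0.00005, 0.0042, 0.0194) applied at the actual looks: 0.0523.

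Binomial simulation at an 18% ROSC rate gives 0.059, but a single pooled z-test at 100 per group already gives 0.051, so part of that figure is discreteness. Extending to at most 150 per group under 9.3 adds almost nothing (0.0587 without, 0.0589 with).

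**Second trigger.** The protocol gives neither the correlation between the two test statistics nor 30-day survival in the eligible cohort, so both are assumed. The calculation also assumes that a crossing always stops the trial and that a survival crossing counts as positive.
- Correlation 0 to 0.7, final at 0.05: chance of any false positive 0.078 to 0.092.
- Same, final level corrected: 0.072 to 0.085. The error of the ROSC test itself is then 0.047 to 0.0495.
- Survival 4% to 14%, nested within ROSC, final at 0.05: 0.065 to 0.086.

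**Power at 18% versus 36%, 100 per group.** With the final test at 0.05 after the looks: 0.827 (pooled variance) or 0.842 (unpooled). With the corrected scheme: 0.808 or 0.824. The loss is 1.9 or 1.8 points. A single-look test at 0.05 has 0.818 or 0.833, so against that design the loss is about 1 point.

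**The case against.** Section 9.6 never mentions the final analysis. It can be read as setting 0.05 for the whole trial, with O'Brien-Fleming distributing it; ROSC is then not inflated. Chapter 9 also promises a separate SAP before the first interim, where boundary values would normally stand. This has weight: a reader might infer that the protocol fixes the final test at 0.05, and it does not say so outright. The contrast with the interim analysis in 9.6 and the unadjusted 0.05 in 9.2 and 9.3 still make that the plainer reading.

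A reader might also infer that the survival trigger pushes the ROSC test above 5%. It does not, and ROSC is the only hypothesis in 9.1. The 7% to 9% is the chance of a false crossing on either endpoint, and the rule in 9.3 is advisory. The 14% end of the survival range is the national rate for all arrests; with 18% ROSC it would mean that 0.14/0.18 = 78% of ROSC patients survive. At 8% survival the figure is still 0.067 to 0.083.

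Section 11.3 permits a stop on the primary endpoint without excluding others, and 30-day survival may be shorthand for the mRS-based secondary endpoint. That softens the inconsistency, but the terms still differ within 9.3.

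Finally, a reader might infer that investigators would see comparative results. No section says who receives unblinded tables, the analysing statisticians are blinded, and information flow is left to a DMC charter that is not shown. The routing point is therefore conditional.

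**Conclusion.** The point holds as a defect of wording with a modest numerical consequence. If the final ROSC test is run at 0.05 after three O'Brien-Fleming looks, overall two-sided error is about 5.7% (5.2% with equal-look boundaries, up to about 6% with Lan-DeMets spending). This assumes the normal approximation and that boundary crossings are acted on. If 0.05 was meant as the overall level, there is no inflation for ROSC; the text has to say which is meant.

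The inconsistency in the stopping endpoint does not depend on how 9.6 is read. Its consequence is a chance of roughly 7% to 9% of any false-positive stop or claim, conditional on the assumed survival rates or correlations, on the advisory rule being followed, and on a survival crossing counting as positive. The sample size of 100 per group is not in question.

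**What to change.** 1. In 9.6, state that 0.05 is the overall two-sided level for the primary endpoint across all interim analyses and the final analysis.
2. Use one O'Brien-Fleming scheme for 30, 60, 90 and 100 per group: nominal p about 0.0002, 0.0083, 0.031 and final 0.041. If Lan-DeMets spending is preferred, specify the function; the final level is then about 0.036 to 0.039.
3. Make ROSC the only formal efficacy stopping endpoint, with 30-day survival with mRS 0-3 as supportive information. Use the same terms in the opening of chapter 9 and in 9.3, 9.6 and 11.3.
4. State in 11.3 and the DMC charter that unblinded interim results go to the DMC, which recommends directly to the sponsor.

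Settle all four before the first interim. The cost is wording only: no added patients, and power at 18% versus 36% falls by under 2 points to about 0.81 to 0.82, still above 0.80.

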## Expected drop out rates

The randomisation and intervention are performed before informed consent can be obtained. Due to earlier experience with studies in our centre involving cardiac arrest patients and deferred consent ^47^, and the experience from the pilot trial, we expect a very low drop-out rate. The estimate is therefore set to 5%.

## Specification of exploratory subgroups

This is the first large dataset to be collected on this intervention. Any subgroups that may have enhanced or reduced effect of the intervention is currently unknown. To assess the possible modifiers of the intervention effect, the following exploratory analyses will be used:

- Age
- Sex
- Type of initial rhythm (VF/VT or PEA/AS)
- Time from debut of arrest to aortic occlusion
- Study site
- Type of catheter used
- Hypoxemia as probable cause of arrest

These will be analysed using generalised linear models. This includes multiple regression analyses, which enable multiple imputation if necessary.

## Treatment of missing data

Missing data will be reported in the primary publication.

There will be no missing data on the primary endpoint, due to the design of the case report form.

Multiple imputation will be considered if substantial amount of data is missing.

## Min/max number of subjects per centre

No minimum or maximum number of subjects per centre is set.

# Project methodology and overall design

The purpose of the study is to assess the efficacy of REBOA as an adjunct treatment in non-traumatic cardiac arrest and the effects of this intervention on ROSC. This is not a trial to test any medical device, nor to compare the effect of different REBOA catheters.

This is a prospective, randomised, parallel group, multi-centre, phase II clinical trial. Patients are randomised in a 1:1 ratio to be included to the control group or the intervention group (Figure 3). The control group receives ACLS according to national guidelines. The intervention group receives ACLS according to national guidelines and the REBOA procedure as an adjunct treatment.

[figure not shown]

*Figure 3. Flow-chart of patient allocation*

Because of the nature of the intervention, it is impossible to blind the performer of the REBOA procedure. Further is it not practically possible to blind the patient for treatment group. Statisticians that perform the analysis of primary and secondary endpoints will be blinded.

The research project is estimated to last for 10 years. This includes start-up and education of the study centres, enrolment of patients, evaluation of last included patient one year after randomisation and five years retention period of study documentation.

## Randomisation procedure

Patients will be allocated in a 1:1 ratio between the two study groups. A permuted block randomisation method stratified by site will be used to allocate eligible patients to either the control group (treatment 1) or the intervention group (treatment 2). This will be as sealed envelopes to be selected on scene if the patient is eligible for randomisation. Each site will have envelopes in each appropriate intervention kit (one in each either helicopter, rapid response car or both). Randomisation will be performed by KlinForsk, Clinical Research Unit, Central Norway. The random allocation sequence is generated using a Microsoft Access data base by KlinForsk. No investigator has access to the allocation sequence.

The envelopes will not be able to see through or open without breaking the seal. The envelopes will be collected by members of the project management and distributed to the site investigator on each study site for placement in the REBOA study kit. An accountability form for all envelopes will be in place. Unopened envelopes will be returned to KlinForsk.

## Medical devices in the study

In advanced cardiovascular life support several medical devices are used for treatment and diagnosis. All these devices will be used on patients in both groups of this trial. Product specifications and exact producers/ product numbers/ batch codes of devices other than REBOA catheters will not be recorded. The sponsor of this trial takes no responsibilities in the funding, provision, approval or other aspects regarding devices other than the REBOA catheters in this trial.

### Medical devices in both groups

- Mechanical chest compression systems
- Monitoring equipment
- Cerebral oximetry equipment
- Defibrillators
- Ultrasound
- Central and peripheral venous catheters
- Arterial catheters
- Intraosseous needles
- Endotracheal tubes
- Supraglottic airways
- Bag and mask for ventilation
- Others

### Medical devices in the intervention group only

In addition to equipment used in both groups, a REBOA balloon catheter and procedure kit will be used. Several balloon catheters are available. Currently, two catheter types are considered for use in this trial:

- the REBOA Medical TM 20 mm balloon, REBOA Medical AS
- the ER-REBOA Catheter, Prytime Medical

Product information and instructions for use are attached (appendix 29.3).

Other catheters, e.g. the Tokai Occlusion Balloon Catheter or any new catheters from different producers that may be available during the trial period, will be considered for use. All catheters will be used according to the CE/FDA approval.

It is an obvious advantage that the same equipment is used both pre-hospital and in-hospital at a study site. Local variations in in-hospital use can therefore dictate a change in catheter type at a study site. This will be decided by agreement of the hospital in question, the site investigator and the sponsor.

### Kit for REBOA intervention

The necessary equipment to perform the REBOA procedure is gathered in a procedure kit. This is as supplied by the manufacturer (Prytime or Reboa Medical) and is not altered. The kits are identical on all study sites using the Prytime or Reboa Medical catheter, respectively.

The study equipment (catheters and REBOA kit) will be clearly labelled “for REBOARREST trial purposes only”, see label in appendix, chapter 29.4.

A separate system for accounting of all catheters will be in place at each study site. The site investigator or designee (SI) has the responsibility for proper handling and storing of the REBOA equipment at each study site. This includes follow-up that enough equipment is in stock. The REBOA kit contains all necessary equipment to perform the procedure. When needed, the SI contacts the project management to order supplies of equipment.

Other necessary equipment (chapter 10.2.1) is considered standard equipment handled at the study sites according to their normal routine. The study equipment will only be used to perform the procedure in subjects included in the clinical study. If the equipment is used for other indications at a study site, the sponsor takes no responsibility for the performance of the equipment or the patient’s outcome.

## Expected duration

The study trial period for each patient is one year after randomisation. After 30 days, the survival rate and adverse reactions during this 30-day period will be reported. After one year a chart review will be performed to assess all-cause mortality.

The trial is expected to open first site winter 2020/2021. Inclusion of patients is estimated to take three years. Data registration, patient follow up one year after last inclusion and five-year data retention period necessitate a total study period of 10 year.

# Study procedures

Treatment 1 – the control group

The control group will receive treatment as described in the guidelines from the European Resuscitation Council^10^, the Norwegian Resuscitation Council^9^, and other local national guidelines.

Treatment 2 – the intervention group

The intervention group will receive the same treatment as the control group. In adjunct, this group will receive the intervention resuscitative endovascular balloon occlusion of the aorta (REBOA).

The insertion of the CE/FDA-approved catheter will follow the procedure as described from the producer. Other catheter that may be used during the trial period will be inserted according to the procedure described from the producers. The instructions for use for each of the currently used catheters are attached (appendix 29.3).

An outline of the REBOA procedure is described in section 11.1.2.

## By Visit

### Before Treatment Starts

**Education and training of personnel**

All involved personnel are regularly part of resuscitation teams both in real life and in training scenarios. This trial will therefore not include any mandatory additional training in standard ACLS.

The pilot study ^1^ demonstrate that the REBOA procedure is feasible in the patient cohort. The P-EMS crew had participated in a structured educational program ^48^. A similar educational program will be held in all study sites and all performers (physicians and paramedics) must complete and pass this program before they can perform the procedure in study subjects. A certificate of approval will be handed to all personnel that complete the program.

All study sites will be equipped with the necessary cannulation equipment and a training dummy to facilitate regularly procedure training during the trial period.

### During Treatment

**Outline of a REBOA procedure at an out-of-hospital cardiac arrest**

The ambulance personnel and the P-EMS crew establish ACLS as per national guideline at site. Either manual compressions or a mechanical chest compression is used. Airway management is handled by either endotracheal intubation or a supraglottic airway device. Intravenous or intraosseous access on the upper body is established. Cerebral oximetry is used, if available. If the patient is eligible for inclusion, the patient is randomised by that the physician opens the next numbered sealed envelope from the REBOA equipment. The randomisation procedure is described in section 10.1.

The paramedic prepares the REBOA-equipment, while the physician prepares the ultrasound machine and examines the patient for visible femoral vessels. Most physicians are right-handed and therefore will prefer to cannulate the patient’s right femoral artery, while placed on the patient’s right side. The paramedic prepares the equipment at the patient’s foot. The femoral inguinal area is washed with antiseptic and a sterile drape covers the patient, from abdomen to distal.

Arterial cannulation is performed ultrasound guided, with out-of-plane technique (Figure 4).

[figure not shown]

*Figure 4. Ultrasound guided femoral arterial cannulation*

After the femoral artery and vein is identified, the artery is cannulated with a 19 G needle and a flexible guidewire is inserted 60 cm. The cannulation can be performed in the ventilation phase of CPR or a 10-20 second pause in chest compression is allowed for. This hands-off time is considered common practice. After the guidewire is placed, the needle is removed, and ultrasound images of the guidewire position is obtained and stored. A scalpel is used to make a small incision next to the guidewire, to widen the entrance point. A 7 Fr introducer sheath is inserted over the guidewire and the stylet is removed (Figure 5).

[figure not shown]

*Figure 5. Insertion of introducer in femoral artery*

If the catheter in use is the ER-REBOA catheter, the guidewire is also removed, and the balloon sheath is placed. If the catheter is the REBOA Medical balloon, the guidewire will remain and the catheter is placed over the guidewire, through the introducer. The balloon sheath is inserted 50 cm for a Zone 1 aortic occlusion (Figure 6) ^49^, by use of measure marks on the catheter. Zone 1 is favoured for best haemodynamic effect ^49,50^.

[figure not shown]

*Figure 6. Zone 1 aortic occlusion*

If applicable, arterial pressure measurements from the distal tip is obtained. Pressure transducer is prepared as per standard routine. Before the balloon is inflated, a palpable pulse check in left radial artery is performed. The balloon is then inflated with 0.9% NaCl or until resistance is felt (max 15 ml if REBOA Medical balloon and max 8 ml if ER-REBOA balloon). The radial pulse check is again performed. If a palpable pulse is present, the location of the balloon is accepted. If a present pulse disappears after balloon inflation, the balloon is deflated, the balloon sheath is withdrawn 5 cm and inflation/pulse check is performed. When in place, the introducer is sutured to the skin and the balloon sheath is attached to the patient’s leg/clothes using tape, clamp or other available equipment.

Invasive blood pressure is measured continuously before and after balloon inflation, when applicable.

If ROSC is achieved, the balloon is slowly deflated, over 30 seconds. Post-ROSC treatment is then performed as per standard routine.

The decision to discontinue resuscitation efforts are performed as per national guideline at site, regardless of the patient’s inclusion in this trial.

The physician must complete a checklist (appendix 29.5) before leaving the scene. This includes these items: Inclusion/exclusion criteria, Video of guidewire placement stored (if applicable), Arterial pressure curves registered (if applicable), EtCO2 measurements noted and ROSC (yes/no).

